#### Sample Size Projections

A priori sample size was calculated using data from the pilot study comparing pain and disability measures pre and post–self-management PE interventions for 19 seafood workers [39]. For each participant and pain or disability outcome, averages of 4 baseline measurements and 2 postintervention measurements were used to calculate the difference in pre- to postintervention outcomes. Mean changes over a control period are assumed to have a mean 0 difference but share the same SD as the intervention period. Changes over the 2 periods for the same person are assumed to be independent. Data were simulated from a simple linear mixed model (LMM):

*Y_ijk_* = α*_i_* + β_1_*X_ijk_Z_ijk_* + β_2_(1 – *X_ijk_*)*Z_ijk_* + ε*_ijk_*

In this model equation, *Y_ijk_* is the outcome of observation period *k* of individual *j* in cluster *i*, *X_ijk_* indicates the intervention group (1: video + support, 0: video), *Z_ijk_* indicates the intervention period (1: intervention period, 0: baseline period), α*_i_* is the random intercept of cluster *i*, and ε*_ijk_* is the error term. The variance of α*_i_* was set as 5% of ε*_ijk_*, such that the intraclass correlation is close to 0.05. For each set of simulated data, a generalized estimation equation model was used to test the null hypothesis β_1_=0. We ran 1000 simulations to calculate the power for each of the different settings of the number of clusters and cluster sizes. Table 1 shows the power based on individual randomization. Fitting a LMM yielded comparable results. The planned enrollment of 102 participants (24 clusters) will provide adequate power for the primary outcomes, pain with most difficult work activities and total disability. An additional 20% enrollment for attrition results in a total anticipated sample of 30 clusters and 122 participants (teams of 3-5 participants) for the comparative effectiveness goals.

**Table 1 table1:** Statistical power (%) based on individual randomization for differentiating between the 2 implementation groups using preliminary data.

Number of clusters	Cluster size	Projected Sample size	Power (%) calculated using results from Dunleavy et al. [39].			
			Pain with most difficult work activities (mean –16.1, SD 18.8)^a^	Average pain (mean –5.2, SD 17.3)^a^	Total disability (mean –2.5, SD 3.5)^a^	Difficulty level with most problematic work activity (mean 9.0, SD 28.5)^a^
**20**						
	3	60	96.9	28.4	88.7	33.8
	5	100	99.8	43.9	98.3	49.5

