### Data Analysis

#### Aim 1

LMMs or generalized linear mixed models (GLMM) will be used to compare within-subject changes in the primary and secondary outcomes (1) over time (baseline, pre, and post) between the intervention periods and the control period and (2) between video and video + support interventions, depending on the distributional feature of the outcome. A general regression structure will be used:

*g*(*EY_ijk_*) = α*_i_* + *γ_j_* + *β’X_ijk_*

In this equation, *Y_ijk_* is the change of the outcome over observation period *k* of individual *j* in cluster *i*; *g*(*EY_ijk_*) is the link function for the mean of *Y_ijk_*; α*_i_* and *γ_j_* are random intercepts specific to cluster *i* and individual *j*, respectively; and *X_ijk_* and *β* are vectors of covariates and associated coefficients. *X_ijk_* indicates intervention (1: intervention video+support, 0: control video only), and baseline characteristics (demographics, occupation, and baseline pain or disability levels). For continuous outcomes that are symmetrically distributed (after transformation), the following traditional LMM will be used:

*Y_ijk_* = α*_i_* + *γ_j_* + *β’X_ijk_* + ε*_ijk_*

where ε*_ijk_* are normal random errors. For skewed continuous outcomes, a GLMM with a gamma distribution will be used. Intervention effects will be represented by mean differences in the continuous outcome between the comparison groups. For categorical outcomes such as prevalence of chronic high impact pain, we will either dichotomize the outcome and fit a logistic mixed model or directly fit a Bayesian multinomial logit model that is available in the R package. Intervention effects will be represented by odds ratios. We will also reparameterize the model to obtain relative risks for measuring intervention effectiveness. These models will account for correlations within each team, as well as within each subject. Results will be verified by general estimating equation models in case within-team or within-subject correlation structures are mis-specified. Missing values for either outcome or covariates will be managed by multiple imputation or the Expectation-Maximization algorithm.

#### Aim 2

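### The gamma mixed model planned for skewed outcomes cannot be fitted to the response the plan defines, a change score whose assumed mean is zero or negative for the primary outcomes

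*Protocol article*

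**What the plan says.** In the Protocol article, Data Analysis, Aim 1, the mixed models "will be used to compare within-subject changes in the primary and secondary outcomes". The text under the general regression equation fixes the response: Y for period k, individual j and cluster i "is the change of the outcome over observation period" k.

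Two branches for continuous outcomes follow:

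- Symmetric: "For continuous outcomes that are symmetrically distributed (after transformation), the following traditional LMM will be used".
- Skewed: "For skewed continuous outcomes, a GLMM with a gamma distribution will be used".

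The effect measure for both is then given: "Intervention effects will be represented by mean differences in the continuous outcome between the comparison groups".

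The Sample Size Projections section works on the same scale. It assumes: "Mean changes over a control period are assumed to have a mean 0 difference but share the same SD as the intervention period". Table 1 takes its intervention-period changes from the pilot study, for example "Pain with most difficult work activities (mean –16.1, SD 18.8") and, for total disability, mean -2.5, SD 3.5. These are the two outcomes that the section names as primary.

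**The concern.** A gamma distribution puts probability only on values above 0. A change score is free to be negative, zero or positive, and the trial hopes that pain and disability changes will be negative. The response and the distribution are set a few sentences apart in the same section and do not fit together.

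At stake is the prespecified handling of any pain or disability outcome whose changes turn out to be skewed. If a primary outcome falls into that branch, the named model will not run, and a replacement would have to be chosen after the data are seen. That choice can move the estimate.

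**Working it through.** **Inputs.** Control-period mean change 0, with the same SD as the intervention period (Sample Size Projections). Intervention-period mean change and SD (Table 1): task pain -16.1, 18.8; total disability -2.5, 3.5; average pain -5.2, 17.3; difficulty with the most problematic activity +9.0, 28.5.

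**1. Are these really the change scores behind the plan's power figures?** In the stated simulation model, the test of β₁ = 0 compares the support arm's intervention-period changes (n/2) with all control-period changes (n). Two-sided alpha 0.05 is assumed here, as the article does not state it. For 20 clusters of 3 (n = 60):

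- Task pain: SE = 18.8 × √(1/30 + 1/60) = 4.20; 16.1/4.20 = 3.83; power = Φ(3.83 - 1.96) = 96.9%. Table 1 gives 96.9%.
- Disability: SE = 3.5 × √(1/30 + 1/60) = 0.783; 2.5/0.783 = 3.19; power = Φ(3.19 - 1.96) = 89.1%. Table 1 gives 88.7%.

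The plan's figures reproduce for both primary outcomes, so the means and SDs are being read on the intended scale.

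**2. Argument that needs no distributional assumption.** A gamma mean is always above 0. The assumed means are 0 (control period), -16.1 and -2.5 (intervention period). None is possible for a gamma variable. Also, any variable with mean 0 and a non-zero SD must take some negative values, so control-period changes alone break the model.

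**3. Illustration of size, assuming normal changes.** P(change ≤ 0) = Φ(-mean/SD):

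| Outcome | Intervention period | Control period | One period of each, averaged |
|---|---|---|---|
| Task pain | Φ(16.1/18.8) = Φ(0.856) = 80.4% | 50% | 65.2% |
| Total disability | Φ(2.5/3.5) = Φ(0.714) = 76.2% | 50% | 63.1% |
| Average pain | Φ(5.2/17.3) = 61.8% | 50% | 55.9% |
| Difficulty item | Φ(-9.0/28.5) = 37.6% | 50% | 43.8% |

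**4. Does reversing the sign help?** No. With improvement scored as positive, 100 - 80.4 = 19.6% of task-pain changes and 100 - 76.2 = 23.8% of disability changes in the intervention period still lie below 0. So do half of the control-period changes, and their mean is still 0.

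**5. Does anything else in the section repair it?** The bracketed reference to transformation belongs to the symmetric branch. No shift is stated for the gamma branch. The planned check by estimating equations is offered for mis-specified correlation structures, not for the response distribution.

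**The case against.** The best defence is that this is loose drafting in a condensed article. The section says that the model depends on the distributional features of the outcome, and outcome there may mean the score at a visit rather than its change. A shift could also be fixed in advance from the scale limits, and such details usually sit in the SAP. This explains how the sentence may have arisen, but the only definition of Y in the section is a change. The protocol has already named both the response and the family, and an SAP that follows the text inherits the conflict.

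Second, the percentages assume normality, and normal changes would go to the linear mixed model and never reach the gamma branch. This stands. The percentages are illustrative, and the conclusion rests on the assumed means alone.

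A reader might infer more than the article supports:

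- *That changes are mostly zero or negative for every outcome.* The difficulty item has a pilot mean of +9.0, with about 38% at or below 0 in the intervention period under normality.
- *That the logistic model has the same fault.* That sentence speaks of prevalence and of a dichotomized outcome; it does not say that a change in status is modelled.
- *That a gamma model would yield ratios and contradict the stated mean differences.* No log link is named. An identity link gives differences directly, and marginal differences can be derived from other links.
- *That improved workers would be dropped from the analysis.* Nothing in the article proposes this.

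**Conclusion.** The point holds as an internal contradiction in the Aim 1 analysis section: for the two primary outcomes, the fallback for skewed data is incompatible with the response it is meant to model. This follows from the plan's own mean changes (0, -16.1, -2.5) and the definition of the gamma distribution. It does not depend on the shape of the data. The 80%, 76% and 50% figures do assume normality and only indicate how far from workable the rule is.

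The reach is limited. Only the skewed-outcome branch is affected. The linear mixed model is valid for change scores, and no power or sample size figure changes. The sentence should be corrected before analysis, but it does not threaten the design.

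**What to change.** Preferred: keep the change score as the response and replace the gamma sentence. For skewed changes, use the same linear mixed model, or the generalized estimating equations already planned as a check, with robust standard errors. Report mean differences, as the plan already intends. With 24 clusters planned for analysis, a small-sample correction to the robust standard errors is worth naming at the same time.

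Alternative: keep a gamma-type model, but state that it is fitted only to visit-level scores that are strictly positive. Name a method that allows zeros for scales where they occur, and report marginal mean differences. This changes the response for that branch, so the visit and arm-by-visit terms would also have to be written out. Redefining the response for all models is not needed.

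The preferred option costs one or two sentences in the protocol or SAP. It needs no new data and no change to enrolment. The Results section reports 14 workers enrolled by December 6, 2024, with data collection ending in late 2027 or early 2028, so the change can be made well before the outcome data are complete.

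### The Aim 1 change-score model cannot represent a negative correlation between control-period and intervention-period changes, so the within-subject test can exceed 5% (up to about 11%, depending on that correlation)

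*Protocol article*

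**What the plan says.** In the protocol article, Data Analysis, Aim 1, the modelled quantity "is the change of the outcome over observation period" k for a worker in a team. The first comparison is "over time (baseline, pre, and post) between the intervention periods and the control period"; the second is between the two arms. The two non-residual stochastic terms "are random intercepts specific to cluster" and individual, and for continuous outcomes the remaining terms "are normal random errors". The section then states: "These models will account for correlations within each team, as well as within each subject". The next sentence adds a check of the results by estimating equations, in case the team or subject correlation structure is wrong.

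Sample Size Projections makes a related assumption: "Changes over the 2 periods for the same person are assumed to be independent". It also says: "Mean changes over a control period are assumed to have a mean 0 difference but share the same SD as the intervention period". Power there is for a GEE test of beta1 = 0, the intervention period under video + support against the baseline period.

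**The concern.** Each worker has one pre-intervention score. It closes the control period and opens the intervention period. A pre score that is high by chance makes the control-period change look like worsening and the intervention-period change look like improvement; a low one does the reverse. The two changes of one person therefore tend to be negatively correlated.

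A random intercept for the individual adds a shared, non-negative variance to both changes, so it can only represent a correlation of zero or more. When the true correlation is negative, its variance is estimated at zero and the model treats the two changes as independent. The statement about within-subject correlation then fails for this outcome, and the standard error of the period contrast is too small.

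At stake is objective 1. Both arms view the videos, so the comparison with the within-subject control period is the only quantitative test of whether self-management works at all. The error makes that test too liberal.

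**Working it through.** **Inputs.** From Sample Size Projections and Table 1: change in pain with the most difficult work activities, mean -16.1, SD 18.8; total disability, mean -2.5, SD 3.5; equal SD in both periods; team intraclass correlation 0.05; 102 workers in 24 teams. From Target Enrollment and Randomization: 1:1 allocation. Assumed here because not stated: the two-sided 5% level, and the correlation r between the two changes.

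**Reproducing Table 1.** beta1 compares the intervention-period mean in n/2 workers with the control-period mean in all n. With independent changes, Var = SD²(2/n + 1/n) = 3 SD²/n, and power = Phi(|mean|/(SD·sqrt(3/n)) - 1.96).
- Pain, n = 60: 16.1/(18.8 × 0.2236) = 3.83; Phi(1.87) = 96.9% (stated 96.9%; GEE simulation 96.8%).
- Disability, n = 60: 2.5/(3.5 × 0.2236) = 3.19; Phi(1.23) = 89.1% (stated 88.7%; GEE simulation 88.6%).

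The columns for these two primary outcomes reproduce within 2 points in every row, which supports the 5% level.

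**The correlation.** Let D1 = pre - baseline and D2 = post - pre, with equal score variance s².
- Equally correlated scores (correlation rho): Var(D) = 2s²(1 - rho) and Cov(D1, D2) = -s²(1 - rho), so r = -0.5 whatever rho is.
- AR(1) scores: Cov = -s²(1 - rho)², so r = -(1 - rho)/2. This is -0.25 at rho = 0.5, -0.10 at rho = 0.8, and tends to 0 as rho tends to 1.
- Person-specific trends plus occasion error: Cov = slope variance - error variance. With slope variance half the error variance, r = (0.5 - 1)/(0.5 + 2) = -0.2. With the two equal, r = 0.

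**Type I error when the model treats D1 and D2 as independent.**
- Pooled period test: the model uses 2 SD²/n and the truth is 2 SD²(1 - r)/n, so the error is 2(1 - Phi(1.96/sqrt(1 - r))).
- Arm-specific beta1 test: the model uses 3 SD²/n and the truth is (3 - 2r) SD²/n, so the error is 2(1 - Phi(1.96/sqrt((3 - 2r)/3))).

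| r | Pooled period test | Arm-specific beta1 test |
|---|---|---|
| 0 | 5.0% | 5.0% |
| -0.10 | 6.2% | – |
| -0.25 | 8.0% | 7.0% |
| -0.50 | 11.0% | 9.0% |

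At r = -0.5 the true pooled standard error is sqrt(1.5) = 1.22 times the model's, so the model's is 1 - 1/1.22, about 18%, too small.

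**Simulation check** (REML, 102 workers in 24 teams, variances bounded at zero, 2,800 null trials per scenario):

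| Test | Equal correlations (r = -0.5) | AR(1) 0.5 (r = -0.25) |
|---|---|---|
| Pooled period, mixed model | 10.9% | 8.0% |
| Arm-specific, mixed model | 8.1% | 7.5% |
| Between arms, intervention-period change | 4.4% | 5.1% |
| Pooled period, team-clustered GEE, uncorrected robust SE | about 7% | about 7% |

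The individual variance was estimated at zero in 99-100% of these fits. A separate run of 250 null trials gave 6.0% for the team-level GEE. Adding the baseline score as a covariate does not cure the problem (about 11-13% by formula under equal correlations).

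**Power at n = 102, using the correct variance (3 - 2r) SD²/n.** At r = 0: 99.9% for pain and 98.6% for disability. At r = -0.5, Var = 4 SD²/n: pain 16.1/(18.8 × 0.1980) = 4.32, Phi(2.36) = 99.1%; disability 2.5/(3.5 × 0.1980) = 3.61, Phi(1.65) = 95.0%.

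**The case against.** The strongest reply is that the article anticipates a wrong correlation structure and plans GEE for that case. This stands in part. Robust standard errors do not depend on the working correlation, and they bring the pooled test down to about 6-7%. But GEE is planned only as a verification, no rule says which result counts if the two differ, and 24 teams without a small-sample correction leave it somewhat above 5%.

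A second reply is that the errors are called normal, not independent, and that residual covariance may be set in an analysis plan not shown here. That is fair: the finding rests on the usual reading of a random-intercept model, with independent residuals and non-negative variances.

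A third is that r is unknown. This stands in full. A reader might infer a firm rate of 8-11%, but strong serial correlation or person-specific trends could bring r close to zero, and the inflation would then disappear.

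Three further inferences are not supported:
- That the randomised comparison is compromised. The between-arm contrast of intervention-period change runs at about 5%.
- That the trial is underpowered. Independence is openly labelled an assumption, and power remains high without it.
- That workers who miss the pre visit drop out of the analysis. The article plans multiple imputation or the EM algorithm for missing values.

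**Conclusion.** The concern holds for the within-subject period comparison. As written, the model cannot represent the negative correlation that a shared pre score tends to produce, so the statement that within-subject correlation is accounted for is not secured. The type I error of the pooled period test lies between 5% (r = 0) and 11% (r = -0.5) over the patterns examined, and that of the arm-specific test is about 7-9% for r from -0.25 to -0.5. These figures rest on an assumed r, an assumed two-sided 5% level, independent residuals, and variances bounded at zero. Enrolment need not change. The matter is worth correcting because it affects the test of objective 1 in the liberal direction and follows predictably from the design.

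**What to change.** - For continuous outcomes, model the baseline, pre and post scores themselves with an unstructured within-person covariance and a team random effect. Test (post - pre) - (pre - baseline), overall and by arm. Alternatively, keep the change scores but allow a negative residual covariance between a worker's two periods.
- State that small-sample-corrected robust standard errors decide if GEE and the mixed model disagree.
- In Sample Size Projections, replace the independence assumption with a range of negative correlations and restate the power (about 99% for pain and 95% for disability at r = -0.5).

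The cost is wording and model code, with no new data. Standard errors for objective 1 become slightly wider and the stated power slightly lower. The Results section reports 14 participants enrolled by 6 December 2024 and final analysis only after data collection ends in late 2027 or early 2028, so there is time to make the change.

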### Prior Work

This protocol builds from a preliminary study of streamlined individualized participatory ergonomic (PE) methods in clam aquaculture workers with similar physically challenging work [39,41]. Workers with chronic LBP were introduced to ergonomic concepts to reduce risk, selected 3 pertinent and acceptable strategies from a list, reviewed videos, and received text reminders. Significant improvements in disability, work-task pain, pain anxiety, and coping compared to baseline were observed (*P*<.05; n=19), with pain improvements greater than published minimal detectable change for 74% of the participants. The methods were both feasible and acceptable. These promising results led to recommendations to establish whether these approaches are effective in a larger cohort over longer timeframes, in different contexts, and with follow up [39].

We will investigate the effectiveness of self-management and ergonomic individual choices along with behavior change support for nursery and landscape workers. The first aim is to determine if self-management videos combined with multimodal personalized support is more effective than self-management videos alone for improving LBP management among horticulture workers. We hypothesize that compared to the video modules alone, the combined multimodal personalized support will result in (1) greater reductions in work task pain and disability, (2) lower prevalence of high-impact chronic pain, (3) greater reduction in substance use to manage pain, (4) greater reeducation in pain anxiety and depression, and (5) improved coping and self-efficacy. The second aim is to identify contextual factors that impact engagement, adoption, effectiveness, and implementation of nonopioid alternatives for LBP self-management. Understanding the external context and individual and team characteristics will help explain the results, provide important implementation perspectives, and inform translation.

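### For yes/no outcomes, GEE is set to verify a mixed-model odds ratio that it does not estimate, so the size of any gap cannot show a mis-specified correlation structure

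*Protocol article*

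**What the plan says.** All of this stands in the protocol article, Methods, Data Analysis, Aim 1.

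- The general regression structure has two terms, one for team and one for worker, that "are random intercepts specific to cluster" and individual respectively.
- For categorical outcomes, with the prevalence of chronic high-impact pain as the named example, "we will either dichotomize the outcome and fit a logistic mixed model or directly fit a Bayesian multinomial logit model".
- For these outcomes, "Intervention effects will be represented by odds ratios". A second measure follows: "We will also reparameterize the model to obtain relative risks for measuring intervention effectiveness". The article does not say how that is done.
- On dependence: "These models will account for correlations within each team, as well as within each subject".
- One sentence then covers every outcome type: "Results will be verified by general estimating equation models in case within-team or within-subject correlation structures are mis-specified".
- For continuous outcomes the measure is different: "Intervention effects will be represented by mean differences in the continuous outcome between the comparison groups".

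The yes/no outcome belongs to a stated hypothesis. The second item under the first aim (Prior Work) is "lower prevalence of high-impact chronic pain" in the video + support arm.

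**The concern.** The GEE step has one stated purpose, which is to guard against a wrong within-team or within-subject correlation structure. That works as a comparison of estimates only if both methods aim at the same number. Under an identity link they do. Under a logit link they do not: the mixed model gives the odds ratio for a given worker in a given team, and GEE gives the odds ratio in the population of workers. The second lies closer to 1 whenever there is an effect and the random intercepts vary.

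An analyst who compares the two odds ratios may therefore take an expected difference for a fault. Equally, close agreement would not show that the structure is right, because a correct model with large worker variance should produce a gap.

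The same distinction reaches the relative risk, which the article offers as a measure of effectiveness. A relative risk for a worker with average random effects is not the relative risk among horticulture workers, and the article does not say which one it means.

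**Working it through.** **The plan's own figures.** The article gives no prevalence, variance or effect for a yes/no outcome. Its only computed figures are the powers in Table 1, which are for outcomes described by a mean and SD. Simulating the model in Sample Size Projections (two-sided 5% level assumed) gives 96.6% against the stated 96.9% for pain with most difficult activities and 89.8% against 88.7% for total disability, at 20 clusters of 3. The primary columns reproduce, but they do not bear on this point.

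**Model.** logit P(Y = 1 | u) = b0 + b·X + u, with u ~ N(0, s²). X = 1 for video + support. The team and worker intercepts are combined in u. The share of latent variance is ρ = s² / (s² + π²/3), so s² = (π²/3)·ρ/(1 − ρ).

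**Assumptions, none from the documents.** Conditional odds ratio exp(b) = 0.50; population prevalence in the video arm p0 = 0.30; ρ from 0.05 to 0.7. The article's team intraclass correlation of about 0.05 is for a continuous outcome. It serves here only as a low reference point.

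**Steps.**
1. Solve b0 so that the average of expit(b0 + u) over u is 0.30.
2. Average expit(b0 + log 0.50 + u) over u to get p1, the population risk with support.
3. Population odds ratio = [p1/(1 − p1)] / [0.30/0.70]. This is what GEE estimates.
4. Population relative risk = p1/0.30. Relative risk at random effect zero = expit(b0 + log 0.50) / expit(b0).

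| ρ | s² | b0 | p1 | Conditional OR | Population OR | RR at u = 0 | Population RR |
|---|---|---|---|---|---|---|---|
| 0.05 | 0.173 | −0.881 | 0.1795 | 0.50 | 0.51 | 0.586 | 0.598 |
| 0.2 | 0.822 | −0.991 | 0.1893 | 0.50 | 0.545 | 0.578 | 0.631 |
| 0.3 | 1.410 | −1.078 | 0.1963 | 0.50 | 0.57 | 0.573 | 0.654 |
| 0.5 | 3.290 | −1.309 | 0.2120 | 0.50 | 0.63 | 0.560 | 0.707 |
| 0.7 | 7.676 | −1.719 | 0.2311 | 0.50 | 0.70 | 0.541 | 0.770 |

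For ρ = 0.5: (0.2120/0.7880)/(0.30/0.70) = 0.2690/0.4286 = 0.63, and 0.2120/0.30 = 0.707. At u = 0 the risks are 0.2127 and 0.1190, with ratio 0.56.

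**Checks.**
- An exchangeable logistic GEE on 20,000 simulated workers with two observations each, at s² = 3.29 and with nothing mis-specified, gave 0.62 (95% CI 0.59 to 0.65). Theory gives 0.63.
- At ρ = 0.5 the population odds ratio is 0.60 with 15% prevalence and 0.64 with 50%.
- If the conditional odds ratio is 1, so is the population odds ratio. The two methods share the null.
- Converting the conditional odds ratio directly, with p0 = 0.30, gives 0.50/(0.70 + 0.30 × 0.50) = 0.588. At ρ = 0.5 the population value is 0.707.
- With a log link and a random intercept, the factor E[exp(b0 + u)] cancels from the risk ratio, so conditional and population relative risks are equal (0.60 and 0.60 at s² = 0, 0.5 and 1).
- In an identity-link linear mixed model u drops out of the mean difference, so both methods target the same quantity.

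**The case against.** Several points on the other side stand.

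- **The check keeps some value.** The article promises verification but sets no rule that two odds ratios must match. Both methods share the null, so comparing direction and test conclusions remains sound. A reader might infer that the GEE step is useless for categorical outcomes. The text does not support that; only agreement in the size of the effect is uninformative.
- **The relative risk is not shown to be wrong.** A reader might infer that the trial will report a 44% risk reduction (1 − 0.56) where the workforce sees 29% (1 − 0.71). That needs prediction at random effect zero, which the article does not state. Averaging over the random effects, or a log link, removes the excess, and a log link is a natural reading of reparameterizing. An article may also leave this detail to the full plan.
- **The gap may be small.** At a share of 0.05 it is 0.50 against 0.51. Adjustment for baseline pain or disability would absorb some worker variance. Against this, the model has a worker intercept because the same people answer repeatedly, and even a share of 0.2 gives 0.545.
- **The scope is limited.** The two outcomes named as primary for power are continuous. High-impact chronic pain is the only outcome named as categorical; calling substance use a yes/no outcome would be an assumption.
- **A conditional odds ratio is legitimate.** One of the two contrasts is within-subject, so choosing a worker-specific effect is no error. This stands, and it is why the remedy concerns the scale of comparison and labelling, not replacement of the odds ratio.

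**Conclusion.** The point holds for dichotomized outcomes fitted with the logistic mixed model. The stated check sets a conditional odds ratio beside a population-averaged one. With a true effect and non-zero random-intercept variance they differ in a correctly specified model, so the size of the difference cannot reveal a wrong correlation structure.

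For a conditional odds ratio of 0.50 and 30% prevalence in the video arm, the expected population value runs from 0.51 to 0.70 as the latent variance share goes from 0.05 to 0.7. Which end applies is unknown, because the article gives neither a worker-level variance nor a prevalence.

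The relative risk carries a possible overstatement, not an established one. It depends on a computation the article leaves open.

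Direction, the null test and the continuous outcomes under the linear mixed model are unaffected. It is a modest defect in a stated step that concerns a named hypothesis, and worth correcting before analysis.

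**What to change.** For each binary outcome:

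1. Predict each worker's risk from the mixed model under both conditions of the contrast, and average over the estimated random-effect distribution and the observed covariates.
2. Average the GEE predictions over the same covariates, and compare the two methods on that marginal scale. A material difference then calls for an explanation in the model, not in the effect measure.
3. Derive the relative risk from the same averaged risks and say so. If a log link is intended instead, state it.
4. Keep the mixed-model odds ratio if wanted, labelled as conditional on team and worker.

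This does not force a choice between a worker-specific and a population effect. It costs a sentence or two in the plan, a few lines of code (with intervals by the delta method or a bootstrap of teams) and effect sizes that may look slightly less favourable. No new data are needed. With 14 workers enrolled by December 6, 2024 and data collection due to end in late 2027 or early 2028, there is time to settle it.
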